### Study management

2.10

#### Data management

2.10.1

##### Data collection

2.10.1.1

All study results, including clinical and laboratory data, will be recorded in the participants’ medical records and case report forms (CRFs). The researchers are responsible for ensuring that all sections of the CRFs are accurately filled out, and that each piece of information can be verified against source data. Each completed CRF must be dated and signed. Data collection will be carried out by trained research staff, who will adhere to standard operating procedures (SOPs) to ensure the accuracy and consistency of the data. All data will be collected in strict accordance with the research protocol approved by the ethics committee. Participants’ personal information and data will be kept strictly confidential, and all records will use identification numbers instead of personal identifying information.

##### Data storage and archiving

2.10.1.2

The researchers will store all trial data (including participant identification numbers, source data, and researcher documents) and related correspondence materials in the research database. All source data and related documents will be archived for the long term in accordance with applicable laws and regulations after the completion of the trial. Data will be stored in a controlled-access computer system, with access restricted to authorized personnel only, ensuring the confidentiality and integrity of the data. The data will be encrypted to prevent unauthorized access.

##### Data management personnel

2.10.1.3

Data management will be handled by a dedicated research team and data management personnel. The data management team will be responsible for regularly checking data quality to ensure the integrity and accuracy of the data. Every individual involved in data management will receive training and sign confidentiality agreements to ensure adherence to ethical requirements and privacy protection standards. The principal investigator and data management personnel will jointly oversee the data management process, ensuring that data entry and storage comply with the trial protocol.

##### Data disclosure and blinding

2.10.1.4

This study employs a single-blind design, where participants are unaware of their group assignments, while the researchers are informed. Prior to data analysis, the researchers will ensure that the blinding is maintained. All group allocation information will be provided to the relevant personnel in sealed envelopes after the completion of the study. Data analysis will be conducted by an independent statistical analysis team, and the team will not be involved with the group allocation information during data processing and analysis to ensure the impartiality of the results.

##### Data analysis and safety

2.10.1.5

All data will be stored in a secure research database with strict access controls to ensure confidentiality and integrity. During the analysis phase, the data will undergo rigorous preprocessing and cleaning. Missing data will be handled using appropriate statistical methods. All analysis results will be processed using statistical software, and the researchers will follow the pre-established analysis plan. The final analysis results will be reviewed and verified by the statistical team to ensure data accuracy and reliability.

#### Adverse event collection and evaluation

2.10.2

##### Definition and collection of adverse events

2.10.2.1

Although this study involves a behavioral intervention, potential adverse effects or harm to participants must still be considered and monitored. Adverse events in this study include, but are not limited to, negative reactions potentially related to the intervention process, psychological stress, social impacts, or any unintended effects arising from participation.

While the study is considered low-risk, the research team will regularly monitor and collect data on any adverse events throughout the trial period. All participants will be informed that they can report any potential health or emotional adverse reactions at any time during the study. Such reports will be kept confidential, and participants will be encouraged to contact the research team immediately if they experience any negative effects.

Adverse event data will be collected through multiple channels, including face-to-face interviews, self-reported questionnaires, and routine follow-up visits. This comprehensive data collection method will ensure that all potential negative consequences are identified and addressed.

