###### Action plan

2.5.1.2.1

(1) Purpose: enhance patients’ self-efficacy for maintenance(2) Measures: patients will receive 10-min health guidance from the physician via WeChat every Monday. The physician will help patients develop a long-term health behavior improvement plan and provide daily reminders via WeChat. The content of health education topics will be based on multimedia, in the form of articles, pictures, or videos sent to the advance WeChat group. For patients with low adherence, physicians will emphasize the dangers of neglecting animal husbandry hygiene, the risks of infectious diseases, and the benefits of maintaining hygienic habits and adhering to medication schedules. For patients with moderate adherence, physicians will focus on praise and encouragement to help maintain their confidence. For patients with high adherence, physicians will focus on monitoring their progress. Physicians will proactively seek recovery progress from all patients, guide them on the correct use of medication, and encourage active cooperation in treatment. The physician will encourage all patients to fill out the “Health Behavior Diary,” documenting daily health behaviors, issues, and experiences encountered. Patients will also be encouraged to communicate with the physician promptly, and their health behavior progress will be regularly evaluated.

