#### Control group

2.5.2

In the control group, patients will receive the standard discharge education provided upon their discharge from the hospital. As part of this education process, patients will be given a “Brucellosis Health Education” brochure, which contains essential information about brucellosis, including lifestyle recommendations, dietary guidelines, medication instructions, and potential adverse reactions to be aware of. Following discharge, patients will receive a telephone follow-up within a specified period, and an additional follow-up will take place 3 months post-discharge (53). These follow-ups are intended to assess patient progress, adherence to instructions, and any emerging concerns related to their condition.

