##### Anxiety depression ultra short form, PHQ-4

2.8.2.3

The PHQ-4 is a simplified version of the Anxiety and Depression Scale, with two dimensions: depression and anxiety. It consists of four entries, which are scored on a Likert 4 scale (1 = not at all, 2 = for a few days, 3 = for more than half of the days, and 4 = almost every day). Participants are required to assess their experiences of anxiety and depression using this scale. The total score ranges from 4 to 16, with higher scores indicating more severe anxiety and depression symptoms. This concise and easy to understand scale enables medical staff to quickly identify patients with anxiety and depression symptoms and provide an initial assessment. The PHQ-4 has a Cronbach’s *α* of 0.82, demonstrating good internal consistency (58).

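### The article shows no adverse event enquiry that is the same in both arms at fixed times, while clinician contact is far denser in the WeChat arm, so adverse event counts may not be comparable.

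*Protocol article*

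**What the plan says.** Section 2.10.2.1 (Definition and collection of adverse events) names three routes: "Adverse event data will be collected through multiple channels, including face-to-face interviews, self-reported questionnaires, and routine follow-up visits". It adds a spontaneous route: "All participants will be informed that they can report any potential health or emotional adverse reactions at any time during the study". None of these is tied to an arm, and WeChat is not named among them. The same section counts psychological stress among possible adverse events.

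Clinician contact is described separately for each arm:

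- **WeChat arm, Action plan (2.5.1.2.1):** "patients will receive 10-min health guidance from the physician via WeChat every Monday". The physician will also "provide daily reminders via WeChat", patients are encouraged to keep a health behavior diary that includes problems encountered, and "Physicians will proactively seek recovery progress from all patients".
- **Control arm (2.5.2):** "patients will receive a telephone follow-up within a specified period, and an additional follow-up will take place 3 months post-discharge". The purpose is given as follows: "These follow-ups are intended to assess patient progress, adherence to instructions, and any emerging concerns related to their condition".

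Both arms receive the questionnaires at Months 0, 3, 6, 9 and 12 (section 2.1 and Table 1), completed online (section 2.8), and the reminders and regular telephone contact of the retention plan (section 2.6).

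Table 1 lists consent, screening, allocation, demographics and each outcome scale, but no adverse event assessment. Reported events are graded and judged for relatedness by the clinical team and may lead to adjustment of the intervention (2.10.2.2). The data monitoring committee may stop the trial if a pre-defined harm threshold is exceeded (2.11).

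**The concern.** How often an event is recorded depends on how often somebody has the chance to hear of it. A patient who speaks to a physician every week, and is actively asked how recovery is going, has many more occasions to mention a problem than one with two scheduled follow-ups. If nothing else puts the same question to both arms at the same times, a difference in recorded events mixes true harm with opportunity to report.

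The likely direction is more events recorded in the WeChat arm and some missed in control. Section 2.2 says that evaluators know the allocation, so uneven detection could be joined by uneven attribution when relatedness is judged.

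The counts have uses. They can prompt a change to the intervention and they enter a stopping decision. They will also be the trial's evidence on whether a programme that deliberately stresses the dangers of the disease (2.5.1.1.2 and 2.5.1.1.3) has a psychological cost.

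**Working it through.** The protocol states no adverse event rate, no number of adverse event contacts and no harm comparison, so there is no figure to reproduce. The check has three steps.

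**1. Which stated channels are common to both arms, and do they visibly ask about harm?**

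| Channel | Same in both arms? | Adverse event question shown? |
|---|---|---|
| Questionnaires, Months 0, 3, 6, 9, 12 | Yes | No: none in the instruments of 2.8, no row in Table 1 |
| Spontaneous report at any time | Same right; easier with an open clinician channel | Not solicited |
| Retention calls (2.6) | Yes; frequency not stated | Address concerns in general |
| Routine follow-up visits | Not defined; follow-up differs by arm in 2.5 | Control follow-ups cover emerging concerns |
| Face-to-face interviews | No schedule given | Not described |

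**2. Scheduled arm-specific clinician contact during the 3-month intervention**

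- WeChat arm: 1 session per week × 13 weeks = 13, if sessions run throughout.
- Control arm: 1 telephone follow-up + 1 follow-up at 3 months (mode not stated) = 2.
- Ratio: 13 / 2 = 6.5.

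Daily reminders (about 91 over 13 weeks) are left out because they are outbound messages and are not described as enquiries.

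**3. What this could do to the counts (illustration; all detection inputs are assumptions)**

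Let q be the chance that one contact brings out an existing event, the same in both arms, and k the number of further contacts shared by both arms. With contacts treated as independent:

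- P(detected, WeChat) = 1 − (1 − q)^(13 + k)
- P(detected, control) = 1 − (1 − q)^(2 + k)

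With equal true risk, the apparent ratio of recorded events is the first divided by the second:

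| q | k = 0 | k = 2 | k = 5 |
|---|---|---|---|
| 0.05 | 5.0 | 2.9 | 2.0 |
| 0.10 | 3.9 | 2.3 | 1.6 |
| 0.20 | 2.6 | 1.6 | 1.2 |
| 0.50 | 1.3 | 1.1 | 1.0 |

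In patients, take the planned 29 per arm and an assumed true risk of 20%, so 0.20 × 29 = 5.8 affected in each arm. At q = 0.10:

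- k = 0: 5.8 × (1 − 0.9^13) = 4.3 recorded in the WeChat arm, against 5.8 × (1 − 0.9^2) = 1.1 in control.
- k = 5: 5.8 × (1 − 0.9^18) = 4.9, against 5.8 × (1 − 0.9^7) = 3.0.

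The excess shrinks as shared contact or per-contact detection rises, and is negligible at q = 0.50 with k = 5. It does not reverse. The model is generous to the concern in that it treats each event as present at every contact.

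**The case against.** **The stated channels are not arm-specific.** This stands. Section 2.10.2.1 does not say that events are gathered through WeChat, the diary or the reminders. The imbalance follows from setting the contact schedules beside an undefined follow-up route and spontaneous reporting; it is not a rule that the protocol lays down.

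**The control arm has more than two contacts.** This also stands. It shares the 3-monthly questionnaires, the retention calls and any-time reporting, and its own follow-ups cover emerging concerns. A reader might infer that control patients are seen only twice while WeChat patients are monitored daily. The documents do not support that: the figure of two covers arm-specific clinician follow-ups only, and scheduled two-way contact in the WeChat arm is weekly.

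**No harm comparison is planned.** Correct: section 2.9 states no between-arm test of adverse events, and 2.10.2.2 describes case-by-case assessment. A reader might therefore go too far in calling the comparison biased or the control arm under-monitored. What can be said is that the counts may not be comparable.

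**A worsening PHQ-4 would be noticed.** A reader might infer that severe deterioration on an online PHQ-4 leaves no adverse event record. No section says so. Questionnaires are a named source, and section 2.8.2.3 says that the scale "enables medical staff to quickly identify patients with anxiety and depression symptoms and provide an initial assessment". The link is simply not spelled out. Likewise, collection does not fall back on spontaneous reports alone after Month 3, since regular monitoring is stated for the whole trial.

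**An article leaves forms and procedures to the full protocol.** This has weight, and adverse event forms may exist. But Table 1 sets out the assessments down to satisfaction, and the section asserts that its method will identify all potential negative consequences. The schedule shown does not bear that out.

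**Conclusion.** The point holds in a limited form. The article describes clearly unequal clinician contact in the 3-month intervention (about 13 sessions against 2 follow-ups, 6.5 to 1) and shows no solicited adverse event enquiry that is identical in both arms at fixed times. Following it as written can record more events in the WeChat arm, and miss some in control, when true harm is equal.

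The size cannot be derived from the documents. Ratios between about 1.0 and 5.0 rest on assumed per-contact detection (0.05 to 0.50) and an assumed 0 to 5 shared contacts; the patient counts also assume a 20% true risk. The conclusion further assumes that WeChat sessions run weekly throughout and that no common enquiry is fixed in a fuller document. It does not touch the efficacy analysis or the sample size. It is worth correcting because the counts can trigger intervention changes and a stopping decision, and the correction is cheap.

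**What to change.** 1. Add one identical adverse event question set, covering any new health, emotional or social problem since the last questionnaire, to the online questionnaire already sent to both arms at Months 3, 6, 9 and 12. Show it as a row in Table 1.
2. Record the source of every event: solicited at a common time point, spontaneous, or learned through WeChat, the diary or calls.
3. Base any between-arm harm summary on events solicited at the common time points, and list the others separately. All events still go to the clinical team and the committee for safety purposes.
4. Summarise PHQ-4 and PSS-4 changes by arm as a harm measure, since they are already collected equally. Do not record every worsening as an adverse event: without a threshold, a one-point fluctuation would count.

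With the same solicited contacts in both arms, the detection ratio in the model above is 1.00 by construction. The cost is a slightly longer questionnaire, one table row, one field on the case report form and more events to assess. Neither arm's intervention changes.

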##### Adverse event assessment and management

2.10.2.2

All reported adverse events will be assessed by the clinical team to determine whether they are related to the intervention and to classify their severity (mild, moderate, or severe). For each adverse event, the following details will be recorded: the time of occurrence, nature of the event, duration, outcome, and whether any medical intervention is required.

Serious adverse events (SAEs), defined as events requiring medical intervention or those that significantly impact the participant’s health, will be immediately reported to the ethics committee for review. Appropriate actions, including further medical evaluation and adjustments to the intervention if necessary, will be taken in consultation with the ethics committee and healthcare professionals involved in the study.

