### Quality control

2.11

To ensure the integrity and reliability of the data throughout the study, several quality control measures will be implemented. First, double data entry will be employed, where two independent researchers will input the same data. Discrepancies will be flagged and resolved by the study team. Regular data audits will be conducted periodically (e.g., monthly) to check for data consistency, accuracy, and completeness. Any issues identified will be addressed promptly. All research staff will be trained on a standardized data collection protocol to ensure consistency in procedures.

Additionally, a Data Monitoring Committee (DMC) will oversee the data collection process and ensure that any issues related to outliers, missing values, or inconsistencies are addressed promptly. The DMC will be composed of [specific members, e.g., independent biostatisticians, ethicists, and clinical experts], and will operate independently from the study sponsor to avoid any conflicts of interest. Committee members will not have any financial or other interests that could influence their decision-making. The DMC will be governed by a formal charter that outlines its roles, responsibilities, and procedures for overseeing data integrity and compliance with the study protocol. The DMC is responsible for deciding whether the trial should be stopped, particularly if a pre-defined threshold for adverse events or harms is exceeded, in which case the study will be halted for safety reasons.

We will use an electronic data capture system to store all data, which includes built-in validation checks to minimize errors. Finally, quality assurance procedures will be implemented to monitor overall adherence to the study protocol, including informed consent and participant confidentiality. These measures will collectively ensure high-quality, reliable data for the study, minimizing errors and maintaining the integrity of the research findings.

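### The SAE definition makes a mild event serious once it needs treatment, and denser clinician contact in one arm may make adverse event counts non-comparable

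*Protocol article*

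**What the plan says.** Four parts of the protocol article bear on this point.

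- **Seriousness and severity (2.10.2.2).** The clinical team is to judge whether each event is related to the intervention and to "classify their severity (mild, moderate, or severe"). For every event the record holds "the time of occurrence, nature of the event, duration, outcome, and whether any medical intervention is required". The definition of seriousness then follows: "Serious adverse events (SAEs), defined as events requiring medical intervention or those that significantly impact the participant’s health, will be immediately reported", with the ethics committee as recipient.
- **Collection (2.10.2.1).** "Adverse event data will be collected through multiple channels, including face-to-face interviews, self-reported questionnaires, and routine follow-up visits". All participants may also report at any time. No arm is singled out, and WeChat is not among the named channels.
- **Contact with clinicians.** In the mHealth arm (2.5.1.2.1) there is a ten-minute physician session each Monday and a daily reminder. In addition, "Physicians will proactively seek recovery progress from all patients, guide them on the correct use of medication". The control arm (2.5.2) has one telephone follow-up after discharge and one further follow-up at 3 months. Section 2.6 adds telephone contact by the research team, not limited to an arm and without a stated frequency. Section 2.2 says that evaluators know the allocation.
- **Stopping (2.11).** The DMC decides on stopping, "particularly if a pre-defined threshold for adverse events or harms is exceeded, in which case the study will be halted for safety reasons".

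**The concern.** Section 2.10.2.2 treats severity and need for treatment as two separate attributes of every event. It then lets the second decide seriousness on its own. An event graded mild that receives treatment is an SAE by the stated rule, so urgent reports to the ethics committee would mix minor treated events with important ones.

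A second question is whether the counts can be compared between arms. One arm is spoken to by a physician every week and asked how recovery is going; the other is followed up twice. The staff who evaluate know which arm is which. An event is more likely to be noted where someone asks more often, and nothing in the text guards against this. At stake are the meaning of the SAE count, any comparison of harms between arms, and the counts that the DMC sees.

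**Working it through.** **1. The definition against its neighbours in 2.10.2.2.** The article gives no SAE rate, so the check is on the text.

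- Each event has a severity grade: mild, moderate or severe.
- Each event has a recorded item: "whether any medical intervention is required".
- SAE = (medical intervention required) OR (significant impact on health).

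Take an event graded mild, with intervention required and no significant impact on health. The first limb is true and the second false. With OR, the event is serious. The severity grade plays no part. The rule is the same in both arms, so by itself it widens the SAE count in both and creates no imbalance.

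**2. Scheduled clinician contacts in the 3-month intervention.** Taking 3 months as 91 days:

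- mHealth: 91 / 7 = 13 weekly sessions.
- Control: 2 follow-ups.
- Ratio: 13 / 2 = 6.5.

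Daily reminders are left out because they are prompts and not enquiries. Study-team calls are left out because their frequency is not given; they would be added to both arms and pull the ratio towards 1. This is a ratio of contacts, not of captured events.

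**3. What unequal capture could do (illustration; all rates assumed).** Expected events noted = n × true rate × probability of detection. Use n = 29 per arm (2.4) and the same assumed true rate of 20% in both arms, which gives 29 × 0.20 = 5.8 true events per arm.

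| Assumed detection, mHealth / control | mHealth | Control | Ratio |
|---|---|---|---|
| 1.0 / 1.0 | 5.8 | 5.8 | 1.0 |
| 0.9 / 0.8 | 5.8 × 0.9 = 5.2 | 5.8 × 0.8 = 4.6 | 1.1 |
| 0.9 / 0.5 | 5.2 | 5.8 × 0.5 = 2.9 | 1.8 |
| 0.9 / 0.3 | 5.2 | 5.8 × 0.3 = 1.7 | 3.0 |

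The ratio equals the ratio of the two detection probabilities, whatever the true rate. It runs from no imbalance to threefold and depends wholly on figures that the article does not give. In these scenarios the gap comes from events missed in control, not from false events in the mHealth arm.

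**4. The stopping threshold.** Section 2.11 speaks of adverse events or harms. It gives no number and does not say whether SAEs are counted or whether arms are taken singly, together or against each other.

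- If it counts all adverse events, the SAE wording does not change the count, but unequal capture could.
- If it counts SAEs, the broad definition raises the count in both arms.
- If it compares arms, unequal capture matters directly.

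The text does not choose among these.

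**The case against.** A reader might infer that events are captured far more often in the WeChat arm, and that the count behind the stopping rule is therefore inflated in that arm. The document does not support this. The named collection channels and the at-any-time reporting in 2.10.2.1 apply to everyone, the Table 1 questionnaires follow one schedule, and the telephone contact in 2.6 is not limited to an arm. A physician asking about recovery is not a stated adverse event question. More contact may also mean fuller capture in one arm and under-capture in the other, so inflation is not shown. The threshold in 2.11 is not tied to SAEs or to an arm. Its detail may lie in the DMC charter, which is not shown.

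A reader might also infer that nearly everyone will have an SAE, because the Discussion describes brucellosis as often needing prolonged treatment with several drugs. That does not follow: planned treatment of the disease is not intervention required by an adverse event.

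It is also fair to say that a broad definition errs towards more reporting, in a study that 2.10.2.1 calls low-risk. Severity and need for treatment are recorded for every event, so events could be sorted afterwards. No effect on the primary outcome is claimed.

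Two things stand. The seriousness rule is written down and classes a mild treated event as serious; it is not a detail left to another document. And the list of channels in 2.10.2.1 opens with the word including, so nothing keeps events that surface in WeChat contacts out of the counts. Unequal ascertainment remains an uncontrolled risk.

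**Conclusion.** The point holds in two parts of different strength.

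- **Definition: established from the text.** Need for medical intervention is sufficient for an SAE, whatever the severity grade. In neither arm does the SAE count separate serious harm from ordinary treatment. How many events this affects cannot be computed, because the article gives no event rates.
- **Comparability: a plausible risk, not a demonstrated bias.** Scheduled clinician contact differs by about 13 to 2 over the intervention, before the common study-team calls, and evaluators are not masked. The range from 1.0 to 3.0 in the illustration rests on assumed detection probabilities.

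Neither the size nor the direction of any effect on the stopping threshold can be determined from the document. The correction is worth making before events are collected, because it is cheap and later sorting would rest on judgements made by staff who know the allocation.

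**What to change.** 1. Reconcile the seriousness definition in 2.10.2.2 with the severity grades and the intervention item in the same section, and with the ICH-GCP guidelines named in 2.10.4. The text should make clear how seriousness relates to severity and to need for treatment. The clinical criteria are for the investigators and the ethics committee to settle.
2. Add one identical adverse event question to the online questionnaire at each post-baseline visit in Table 1 (months 3, 6, 9 and 12), in both arms. Base any between-arm comparison of harms on the answers.
3. Tabulate spontaneous reports and events that surface in WeChat contacts separately, by source. All events from every source still go to the DMC and the ethics committee; none is dropped from safety oversight.

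The cost is some wording in 2.10.2 and one item on a questionnaire that is already sent at these visits. The small downside is that spontaneous events stand outside the main between-arm comparison, though they are still reported.
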